## Abstract

**Background:**

Older adults with an intellectual disability are at greater risk of increased social isolation, loneliness, and poorer quality of life compared to their non-disabled ageing peers. The MATILDA study aims to improve health and social networks by facilitating older adults with an intellectual disability to engage in their local mainstream community group.

**Methods:**

The 30-month project is a 2-arm, single-blind, randomised feasibility RCT with 1:1 allocation, being conducted in Northern Ireland and London, England. We are aiming to recruit 64 older adults with an intellectual disability (aged 45 plus) who will be randomised to either the MATILDA intervention or an active control group alongside usual care. We will assess feasibility outcomes (i.e. recruitment, acceptability of intervention, retention, etc.). We will also conduct a process evaluation using the Normalisation Process Theory to identify any solutions and challenges in implementing the MATILDA intervention in local community groups.

**Discussion:**

This is a novel, naturalistic experiment, low-cost community intervention that supports older adults with intellectual disability to engage in local community groups. This study builds upon our earlier work in exploring how older adults with intellectual disability age, engage in local community activities, and what are the enablers and barriers to facilitators in joining local community groups.

**Trial registration:**

ISRCTN, ISRCTN15294181. Registered 20th December 2022.

**Supplementary Information:**

The online version contains supplementary material available at 10.1186/s40814-026-01780-3.

## Background

People with an intellectual disability (ID) are living significantly longer than in previous decades, but they experience ageing earlier and at a faster rate than their non-disabled peers [1]. This ageing ID population is predicted to grow four times faster than the general population, placing increasing pressure on health and social care systems [2]. Despite this demographic shift, the needs of older adults with an ID remain underspecified and under-researched.

Unlike non-disabled older adults, chronological age, retirement, and access to pensions do not typically define ageing for adults with an ID [3, 4]. Many have not engaged in paid employment and therefore lack the structural transition points or social markers that signify ageing in the general population [5, 6]. Consequently, they often have limited opportunities to participate in community life alongside their non-disabled peers [7]. This exclusion contributes to loneliness, isolation, and depression, yet neither intellectual disability services nor mainstream ageing services have adequately addressed how to support inclusion for this population [2, 8–13]. Recent UK policy emphasises the importance of community inclusion and social participation for people with disabilities, including the NICE Guidelines (NG96), which recommend ensuring that older adults with an ID have equal access to mainstream services and social opportunities [14–17]. However, the mechanisms by which this can be achieved in practice remain unclear.

### Older adults with an intellectual disability and the impact of loneliness/isolation

Loneliness and social isolation are well-established determinants of poor physical and mental health in the general ageing population [18, 19]. Older adults with an ID face even greater risks due to limited social networks, communication challenges, and negative societal attitudes [8, 9, 20–23]. Petroutsou et al. reported that over half (50.4%) of adults with an ID experience loneliness compared with 10.6% of the general population [21]. This is despite many expressing a desire to remain active and socially connected [20].

Improving social connectedness has proven benefits: meta-analyses in older populations show that interventions enhancing social skills, increasing social support, and creating opportunities for engagement can significantly reduce loneliness [24–26]. Yet, how to translate these approaches to meet the needs of older adults with an ID remains poorly understood.

### Existing approaches: befriending schemes

Befriending schemes have been widely used to address loneliness and isolation, typically involving a volunteer who provides one-to-one social support and companionship. Such schemes can improve perceived social support and psychological wellbeing [27] and may also benefit volunteers through enhanced empathy and community cohesion [28].

However, their effectiveness for people with an ID is uncertain. Small feasibility studies have shown mixed results: Florides [29] reported improved confidence and reduced isolation in a small London-based pilot, while Ali et al. [30] found that despite positive experiences, recruitment challenges limited feasibility. Furthermore, traditional befriending models often rely on short-term, prescriptive relationships that may end abruptly, leaving participants feeling distressed and socially adrift [31, 32]. These schemes tend to provide companionship rather than facilitating long-term inclusion within community networks, and thus do little to address the structural exclusion faced by older adults with an ID.

### Community-based mentoring: the Australian TTR project

The Transition to Retirement (TTR) project, developed in Australia, represents a more embedded, community-based approach [33]. It used active mentoring to support older adults with an ID (aged ≥45) to join existing mainstream community groups. Retired community members acted as mentors, helping individuals with an ID to participate in activities such as bowling, gardening, or crafts. Participants attended groups one to three times per week over 6 months, supported by two to three mentors per participant.

Results were promising: participants reported reduced loneliness, improved wellbeing, and increased social networks. Importantly, many continued attending community groups independently after the study ended, suggesting that community integration was sustainable. The TTR approach thus moved beyond the one-to-one befriending model by focusing on facilitated inclusion within existing community structures.

Nevertheless, the TTR study had limitations. It targeted adults transitioning from supported employment, limiting applicability to the broader group of older adults with an ID who are not in work. The intervention was also implemented within the Australian service context, which differs considerably from the UK in terms of community infrastructure, volunteer culture, and disability services.

### The MATILDA intervention

Building on the TTR model, our team adapted and expanded it for a UK context, developing the MATILDA intervention (Managing Activities Together to Involve older adults with a Learning Disability in their Local Areas). MATILDA maintains the core principle of enabling older adults with an ID to participate in local community groups but introduces several key innovations:Broader inclusion — MATILDA targets all older adults with an ID, not only those transitioning from employment.Mentor pairing model — Each participant is supported by one or two trained community mentors, rather than a single befriender. This reduces pressure on volunteers and fosters more natural network development within the group.Group integration focus — Mentors work within existing community groups (e.g. walking clubs, arts groups) to promote acceptance and inclusion of the person with an ID.Sustainability — By embedding social connections in mainstream settings, MATILDA aims to create lasting friendships and reduce dependency on structured disability services.

In contrast to befriending schemes, which often provide temporary companionship, MATILDA focuses on social integration, helping people with an ID to belong and participate meaningfully in community life. The dual-mentor model enhances support, while community group involvement increases opportunities for naturally sustained relationships. This approach also reduces reliance on costly formal support and leverages existing social infrastructures, aligning with policy goals for inclusive, community-based care.

### Rationale for a feasibility RCT

Given the promising theoretical and preliminary evidence, it is now timely to conduct a feasibility randomised controlled trial (RCT) of MATILDA. This study will test the practicality and acceptability of conducting a full-scale trial to evaluate the intervention’s effects on social connectedness, wellbeing, and quality of life.

Key feasibility questions include:Can older adults with an ID be successfully identified, recruited, and consented through existing service and community pathways?Is the MATILDA intervention acceptable to participants, mentors, and community groups?Can mentoring relationships and community participation be sustained over the study period?Are proposed outcome measures and data collection procedures appropriate and sensitive to change?

The feasibility RCT will also assess the logistics of randomisation, mentor matching, and retention, providing essential data to inform the design and power calculation of a definitive trial. If feasible, MATILDA could offer a scalable, low-cost, and sustainable approach for commissioners and service providers. By using existing community assets and volunteer capacity, it aligns with national strategies to build inclusive, age-friendly communities [32, 34] and to reduce loneliness among people with disabilities. It would also contribute to UK’s broader policy ambitions around personalisation, prevention, and community participation in social care.

Older adults with an intellectual disability represent a growing yet underserved population at high risk of social isolation and poor wellbeing. Traditional befriending approaches, while valuable, are limited by short-term, one-to-one structures that fail to create sustainable community integration. The Australian TTR model demonstrated that active mentoring can effectively embed older adults with an ID in community groups, but adaptation for the UK context is essential.

MATILDA represents an innovative evolution of this model: a community-based, mentor-supported pathway that promotes long-term social inclusion, wellbeing, and sustainability. This feasibility RCT will establish the groundwork for a future definitive trial and, ultimately, for a scalable intervention capable of improving lives while strengthening inclusive communities.

### Aim and objectives of study

The primary aim of this study is to conduct a UK based, multicentre, feasibility RCT to determine the feasibility (i.e. recruitment, consent, matching, retention, dropout etc.), and acceptability of the Matilda intervention for adults with an intellectual disability targeting health, wellbeing and social networks compared to usual care.

We have planned to assess several secondary outcomes including clinical outcomes (i.e. quality of life, anxiety, loneliness) to:Explore the views of the stakeholders (adults with an intellectual disability, carers, and mentors) about the acceptability of the Matilda intervention Determine the appropriateness and acceptability of the outcome measures to older adults with an intellectual disability, carers, and mentors Measure the fidelity of mentors in supporting older adults with an intellectual disabilityEstimate the effect of the Matilda intervention on the outcomes for the older adults with an intellectual disability (health, wellbeing, and social connectedness), family carers (health, wellbeing), and for the mentors (wellbeing, attitudes to people with an intellectual disability) at 6 and 12 months post intervention Provide preliminary information about treatment effects to inform the sample size for a full trialRecord any adverse events and unintended consequences of the Matilda intervention 

## Methods

### Study design

This is a 2-arm, single-blind, randomised feasibility study with 1:1 allocation, which will be conducted in Northern Ireland and London (Fig. 1). Sixty-four older adults with an intellectual disability will be randomly allocated to either the Matilda intervention plus usual care (‘usual care’ in this instance refers to participants attending a day centre or day opportunity setting) or usual care with three group recreational activities with other older adults with an intellectual disability (active control arm). Group recreational activities will involve older adults with an intellectual disability in the active control arm meeting together on three occasions for example for a meal, a coffee or bowling, etc.

**Fig. 1 Fig1:**
[figure not shown]
Study schematic diagram

The intervention will last 6 months. The primary outcome is feasibility (i.e. recruitment, consent, matching, retention, dropout, etc.). Outcome measures will be collated at baseline, 6 months post intervention and 12 months post intervention. We will conduct a process evaluation and a health economic evaluation.

The feasibility trial will run for 30 months (to include start up right through to project close down) to assess recruitment rates and retention for the measuring of the primary outcome at 6 months post intervention and 12 months intervention. This will also allow us to identify any key difficulties and address them in preparation for a potential definitive randomised trial. The two clinical sites, one in Northern Ireland and one in London, will recruit a total of 64 older adults with an intellectual disability during this period. This protocol is reported in accordance with the Standard Protocol Items: Recommendations for Interventional Trials (SPIRIT) guidelines.

### Ethical approval

Ethical approval was received by the Office for Research Ethics Northern 249 Ireland (ORECNI: 22/NI/0067), and research governance was obtained from both sites in Northern Ireland and England.

### Progression criteria

We will apply predetermined progression criteria as set by Avery et al. [34]. This will be based on the feasibility outcome data pertaining to recruitment, matching older adults with an intellectual disability to mentors, retention rates and reasons for attrition, programme attendance, protocol adherence, and the completion of outcome measures. We will monitor recruitment rates in each site. We will have a wide recruitment network from the outset including user-friendly information on how to promote the study and meetings with various local community organisations. We will identify champions in both sites to help study promotion and a process evaluation will take place with stakeholders.

A traffic light system (green, amber, red) will be used to inform whether the study should progress to a full trial, whether revisions are required, or whether it should be stopped. If there is efficacy, and the green progression criteria are met, it would be appropriate to move to a definitive trial, see Table 1.

**Table 1 Tab1:** Progression criteria: a traffic light system

Progression criteria	Red	Amber	Green
1) Recruitment rates of adults with an intellectual disability and mentors who are approached consenting to randomisation across both sites	<39%	40–69%	70% plus
2) Acceptability of and engagement in the Matilda intervention of at least 60% of the adults with an intellectual disability allocated to this arm across both sites	<39%	40–59%)	>60%
3) Acceptability of the matching process, and engagement in the Matilda intervention of at least two mentors for at least 60% allocated to this arm across both sites	<39%	40–59%)	>60%
4) Acceptability of the appropriateness of the outcome measures for at least 60% of the adults with an intellectual disability and their mentors across both sites	<39%	40–59%)	>60%
5) Retention of at least 60% of the recruited adults with an intellectual disability and their mentors at the 6- and 12-months follow-up across both sites	<39%	40–59%)	>60%

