### Consent

Written informed consent must be obtained by the Research Associate (RA) on each site prior to the collection of trial data and the provision of the intervention. It must be assumed that an adult with an intellectual disability has the capacity until proven otherwise. Therefore, it is important that the person is given the information required in a user-friendly format to make an informed decision using reasonable adjustments. Managing on-going consent, including assessment of capacity to consent, will take place using the following steps.

Research Associates will undertake the Good Clinical Practice Course and receive specific training at each site in how to assess capacity to consent and ensure informed consent is maintained throughout the project on a case-by-case basis. All participants will receive an easy read Participant Information Sheet (PIS) and consent form with pictures or symbols to explain the purpose of the study and what is involved. The PIS and consent form have been prepared in collaboration with our PPI representatives. The RAs will clearly explain the decisions to be made about joining the Matilda Project, completing some questionnaires at several time points, being randomised to either the intervention or control arm, and taking part in the process evaluation interview (qualitative study) using the user-friendly PIS or additional media or communication aids if required. The Research Associates will explain what is involved in participating in the Matilda Intervention (joining a community group, being matched to two or three mentors within the group, time commitments) and being randomised to the control group. The Research Associates will assess if the person can retain the information and where appropriate have present a family member or advocate who is familiar with the communication needs of the person with the intellectual disability.

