### Matching of adults with an intellectual disability, mentors, and local community groups

The Volunteer Co-Ordinator and the disability staff in each site will meet with one older adult with an intellectual disability and their carers at a time, to explore the person’s needs, capabilities, interests, and hobbies, to identify a suitable local community group and discuss the logistics of attendance (availability of both the adult with the disability and the mentors, transportation to and from the community group, when and where the older adults and mentors would meet, etc.).

The Volunteer Co-ordinator will support the 1–2 mentors to facilitate the person with the intellectual disability to attend the local community group. This will continue until the mentors feel they are confident in supporting the adult with the intellectual disability, and the adult is comfortable with the arrangements. Support will be individually tailored, with the Volunteer Co-ordinator regularly following up to ensure that the adult with the intellectual disability is attending and actively involved in the community group (visits, phone, text). Mentors and carers will be able to contact the Volunteer Co-ordinator and intellectual disability staff for advice. By their nature, local community groups such as men’s sheds, sporting activities, knitting, or gardening groups vary in their frequency and duration, typically between 1 and 4 h over 1 to 3 sessions per week. The adult with the intellectual disability will be supported by their mentors to attend the group and facilitate their involvement with the group for 6 months.

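### The number of mentors per participant is stated inconsistently, so a permitted one-mentor match cannot count towards progression criterion 3

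*Protocol article*

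**What the plan says.** The protocol article states the number of mentors in four places.

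- **Progression criteria, Table 1, criterion 3:** besides asking that the matching be found acceptable, this criterion looks for "engagement in the Matilda intervention of at least two mentors for at least 60% allocated to this arm across both sites". Red is below 39%, amber 40 to 59% and green above 60%. The traffic light informs whether the study progresses to a full trial, is revised or is stopped.
- **The MATILDA intervention:** "Each participant is supported by one or two trained community mentors, rather than a single befriender". The same section then says: "The dual-mentor model enhances support, while community group involvement increases opportunities for naturally sustained relationships".
- **Matching of adults with an intellectual disability, mentors, and local community groups:** "The Volunteer Co-ordinator will support the 1–2 mentors to facilitate the person with the intellectual disability to attend the local community group".
- **Consent:** participants are told that taking part involves "being matched to two or three mentors within the group, time commitments".

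The section on the Australian TTR project gives two to three mentors per participant for the parent project, the same number as in the consent explanation. No section reconciles these statements or says how a participant with one mentor is scored on criterion 3.

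**The concern.** Feasibility is the primary outcome, and matching is named as part of it. Criterion 3 is the progression rule for matching. If some participants are matched to one mentor, as the intervention and matching sections permit, they cannot count as successes however well the match works. The criterion then mixes two questions: whether matching and engagement succeeded, and which permitted number of mentors was used. An amber or red result could not be read without knowing which of the two produced it. Separately, the consent explanation does not describe the one-mentor arrangement that the delivery sections allow.

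**Working it through.** **The plan's own figures.** For criterion 3 the article gives only the thresholds, so there is no calculation to reproduce. Its one precision figure, a 95% CI of about 46% to 71% for 60% retention among 64, is reproduced by the exact binomial interval for 38/64 (46.4% to 71.5%). The present point does not depend on it.

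**Step 1: which numbers fit which section.**

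| Section | One | Two | Three |
|---|---|---|---|
| The MATILDA intervention | fits | fits | does not fit |
| Matching | fits | fits | does not fit |
| Consent | does not fit | fits | fits |
| Criterion 3 | cannot count | can count | can count |

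Two mentors is consistent throughout. The conflict concerns one mentor (against Consent and criterion 3) and three mentors (against the intervention and matching sections).

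**Step 2: size of the Matilda arm.** 64 participants (Study design) at 1:1 (Randomisation and assignment of interventions) gives 64/2 = 32.

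**Step 3: the highest score on criterion 3.** Let k be the number of participants with one mentor. Assume every assigned mentor engages and every participant finds the matching acceptable. The score is then (32 − k)/32. Green needs more than 0.60 × 32 = 19.2, so at least 20 participants.

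| k | Score | Category |
|---|---|---|
| 0 | 32/32 = 100% | green |
| 12 | 20/32 = 62.5% | green |
| 13 | 19/32 = 59.4% | amber |
| 19 | 13/32 = 40.6% | amber |
| 20 | 12/32 = 37.5% | red |
| 32 | 0/32 = 0% | red |

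Table 1 leaves 59% to 60% unassigned. The value 59.4% is taken as amber because it is not above 60% and rounds to 59%.

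**Step 4: the same delivery under another reading.** If the criterion counted participants whose assigned mentors all engaged, each row above would score 32/32 = 100%, which is green.

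**Step 5: how likely each category is.** The article gives no expected share q of participants with at least two mentors, so a range of assumed values is shown. The number with at least two is taken as binomial (32, q), again with full engagement.

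| q | P(green: 20 or more) | P(red: 12 or fewer) |
|---|---|---|
| 25% | 0.00 | 0.96 |
| 40% | 0.01 | 0.46 |
| 50% | 0.11 | 0.11 |
| 60% | 0.46 | 0.01 |
| 70% | 0.87 | 0.00 |
| 80% | 0.99 | 0.00 |

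The score is therefore sensitive to a matching choice that the delivery sections leave open.

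**The case against.** The strongest reply is that two mentors is the intended model and one is merely tolerated. The intervention section presents a pairing model, contrasts it with a single befriender and calls it dual-mentor. On that reading, whether most participants can be given two mentors is a proper feasibility question, and a progression target may be stricter than the minimum permitted delivery. Red would need 20 of 32 participants (62.5%) without a second mentor, which is arguably what such a criterion should detect. This reading is reasonable, but the article does not state it, and it would not explain the number given at consent. It weakens any claim that criterion 3 is wrong; it does not remove the need to say what the criterion measures.

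Four stronger inferences are tempting, and the article does not support them.

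- A reader might infer that criterion 3 demands two mentors for every participant. It asks for this in about 60% of the arm, so a sizeable one-mentor minority is already tolerated.
- A reader might infer that compliant delivery is bound to fail. That depends on a one-mentor share that is not given. Moreover, amber calls for revision, and the traffic light informs the decision and does not make it alone.
- A reader might infer that the fidelity check shares the ambiguous target. The weekly checklist covers attendance, frequency, activities and adverse events, and no target number of mentors is stated for it.
- A reader might infer that the total number of mentors to recruit is left undefined. Any such total would assume that no mentor supports more than one participant, which the article does not say, and a condensed article may leave that detail to the full protocol.

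A statistical analysis plan could define the scoring. It could not remove a disagreement between the intervention description, the consent explanation and Table 1.

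**Conclusion.** The inconsistency is real and bears on one of five progression criteria. All the statements allow two mentors, but a participant with one mentor complies with the intervention and matching sections and cannot count towards criterion 3. With 32 allocated, full engagement and matching acceptable to all, the highest possible category is green with up to 12 one-mentor participants, amber with 13 to 19, and red with 20 or more. Less than full engagement could only lower the score. How far this matters in practice rests on the one-mentor share, which the article does not give. The Discussion does expect that the availability of suitable mentors may constrain recruitment, so one-mentor matches cannot be dismissed as hypothetical. This is an inconsistency of wording that should be fixed; it does not show that the criterion or the design is unsound.

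**What to change.** Reconcile the intervention section, the matching section, the consent explanation and Table 1 to one statement of mentor number. Which number is right is for the investigators to settle. State explicitly how a participant with one mentor is scored on criterion 3.

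Trial status reports that recruitment was completed in March 2024. Rewording cannot change the consent already given, and altering a predetermined threshold without saying so would be a post hoc change. The reconciliation should therefore be recorded as a dated clarification before criterion 3 is assessed. If that assessment has already been made, the report should say so.

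Report criterion 3 as prespecified. Alongside it, show how many participants in the Matilda arm had one, two and three mentors, and the proportion whose assigned mentors all engaged. A reader can then tell a shortage of second mentors from a failure of matching or engagement.

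The cost is wording and one short table. The planned records of matched numbers (Process evaluation) and each mentor's weekly checklist (Fidelity of intervention) should supply the counts, so no new data collection is expected.

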### Sample size

The chosen sample size is justified based on feasibility outcomes, specifically estimating the proportion of adults with intellectual disability who are recruited and retained. With 64 participants, if observed retention is 60%, the 95% CI for the true proportion retained would be approximately 46% to 71%.

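### The traffic-light bands in Table 1 leave gaps at 39% and at 60%, and the row text (at least 60%) contradicts the green column (>60%)

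*Protocol article*

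**What the plan says.** The Progression criteria section states: "A traffic light system (green, amber, red) will be used to inform whether the study should progress to a full trial". The same section calls the criteria predetermined, and feasibility is the trial's primary outcome.

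Table 1 gives five criteria:

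- **Criterion 1 (recruitment):** red <39%, amber 40–69%, green 70% plus.
- **Criteria 2 to 5:** red <39%, amber 40–59%, green >60%.

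The wording of criteria 2 to 5 sets the target at 60% or more. Criterion 2 begins "Acceptability of and engagement in the Matilda intervention of at least 60% of the adults with an intellectual disability allocated to this arm across both", and criterion 5 reads "Retention of at least 60% of the recruited adults with an intellectual disability and their mentors at the 6- and 12-months follow-up across both sites".

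The article gives no rule for rounding a percentage before it is compared with the bands. The Sample size section takes 60% as its working value: "With 64 participants, if observed retention is 60%, the 95% CI for the true proportion retained would be approximately 46% to 71" per cent.

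**The concern.** A traffic-light table has to give every attainable result one colour. This one does not, in two ways.

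First, adjacent bands do not meet. Red ends below 39% and amber starts at 40%. In criteria 2 to 5 amber ends at 59% and green starts above 60%. In criterion 1 amber ends at 69% and green starts at 70%.

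Second, the description of criteria 2 to 5 includes 60% in the target while the green column excludes it. Criterion 1 uses an inclusive limit, so one table follows two conventions.

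At stake is the advice to progress, revise or stop. If a result falls in a gap, its colour has to be settled by someone who already knows the result, and fixing the criteria in advance was meant to prevent that.

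**Working it through.** **Inputs.** The Study design section says "Sixty-four older adults with an intellectual disability will be randomly allocated to either the Matilda intervention plus usual care" or to the active control, and "This is a 2-arm, single-blind, randomised feasibility study with 1:1 allocation". The adult denominators are therefore 64 overall and 64 × 1/2 = 32 in the Matilda arm. Criteria 2 and 3 refer to the Matilda arm. Criteria 4 and 5 cover both arms; they also name mentors, whose number is not given, so 64 is the adults-only denominator there. The denominator of criterion 1 is the people approached, which is not given either, so no counts can be listed for it.

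**Step 1: the plan's own figure.** 60% of 64 is 38.4 people, and the nearest whole count is 38. The exact (Clopper–Pearson) 95% interval for 38/64 runs from the 2.5% quantile of Beta(38, 27) to the 97.5% quantile of Beta(39, 26), that is 46.4% to 71.5%. This agrees with the stated interval of about 46% to 71%.

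**Step 2: counts against the printed bands of criteria 2 to 5.** All counts from 0 to 64 and from 0 to 32 were classified. The table shows those around the cut-offs.

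| Count | Per cent | Unrounded | Rounded to whole % | Truncated to whole % |
|---|---|---|---|---|
| 24/64 | 37.5 | red | red | red |
| 25/64 | 39.06 | none | none (39) | none (39) |
| 26/64 | 40.6 | amber | amber | amber |
| 37/64 | 57.8 | amber | amber | amber |
| 38/64 | 59.375 | none | amber (59) | amber (59) |
| 39/64 | 60.94 | green | green (61) | none (60) |
| 18/32 | 56.25 | amber | amber | amber |
| 19/32 | 59.375 | none | amber (59) | amber (59) |
| 20/32 | 62.5 | green | green | green |

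Rounding to one decimal place leaves the same three gaps as no rounding. With 32 there is no gap between red and amber: 12/32 = 37.5% is red and 13/32 = 40.6% is amber.

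**Step 3: exactly 60%.** 0.60 × 64 = 38.4 and 0.60 × 32 = 19.2, so exactly 60% cannot occur with the planned adult numbers. It can with other denominators, such as 36/60, if recruitment differs or if mentors are counted.

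**Step 4: how likely the unclassified counts are.** The binomial probability is P(X = x) = C(n, x) p^x (1 − p)^(n − x).

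- n = 64, x = 38, p = 0.60: 0.101.
- n = 32, x = 19, p = 0.60: 0.142.
- n = 64, x = 25: 0.101 if p = 0.40, but 0.0003 if p = 0.60.

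**The case against.** The best defence is that every band is printed in whole per cent, so results would be reported that way. Then 38/64 and 19/32 are both 59% and amber, and the probabilities of 0.10 and 0.14 no longer describe a gap. This stands as far as it goes. It does not rescue the table, because the whole numbers 39 and 60 are themselves missing: 25/64 rounds to 39% and stays without a colour.

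It is also fair that the gaps are narrow, that neighbouring counts are classified, and that the lights inform the decision alongside reasons for attrition, adherence and the process evaluation. That limits the harm. It does not make the printed rule complete or consistent.

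A reader might go further in three ways that the documents do not support.

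- **A joint chance of about 40% that at least one of criteria 2 to 5 falls in a gap.** This multiplies the single-row probabilities as if the criteria were independent. The 32 adults are part of the 64, and engagement and retention are likely to be related. It also needs unrounded percentages, a true rate of 60% in every row, and adults-only denominators in rows that name mentors.
- **Adults and mentors pooled into one percentage, so that one group hides the other.** The wording can equally mean that each group must reach the level. The Quantitative data analysis section defines the consent rate and overall retention on older adults with intellectual disability alone.
- **The sample-size interval is wrong and should read 48% to 72%.** The stated interval is a valid exact one for 38/64. The alternative is a Wald interval at 60% exactly, and the difference of one to two points is a choice of method.

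**Conclusion.** The point holds as an error in the printed rule, and it should be fixed. Two parts need no assumption about rounding: 39% has no colour in any row, and exactly 60% meets the wording of criteria 2 to 5 but is neither amber nor green. With 64 adults the first affects 25/64. The second cannot arise with 64 or 32 but can with other denominators.

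A further part depends on percentages being left unrounded, which the article neither requires nor rules out. Values above 59% and below 60% (criteria 2 to 5), and above 69% and below 70% (criterion 1), then have no colour. For 38/64 and 19/32 the chances are about 0.10 and 0.14, taking a true rate of 60% and adults-only denominators.

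It would be too strong to infer that the table gives no answer near its cut-offs in general. The failures are at specific counts, and those on either side are classified.

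**What to change.** Replace the bands with contiguous ones, applied to unrounded proportions, that keep the protocol's own target of at least 60%:

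- **Red:** <40%.
- **Amber:** ≥40% to <60% (to <70% for criterion 1).
- **Green:** ≥60% (≥70% for criterion 1).

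Print the resulting counts for criteria 2 to 5:

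- **n = 64:** red ≤25, amber 26–38, green ≥39.
- **n = 32:** red ≤12, amber 13–19, green ≥20.

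The cost is a table edit. Against the printed bands read unrounded, 25/64 becomes red, 38/64 and 19/32 become amber, and no count that already has a colour changes it. No new data are needed. The Trial status section reports that recruitment ended in March 2024 and that data collection runs to June 2025. The correction should therefore be dated and, where still possible, made without reference to outcome results; if results were already known, that should be stated.
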